### Addendum 3 - Identification of methylation profiles in cell free DNA in the context of pregnancy related diseases using MeD-seq

#### Introduction

DNA methylation is an epigenetic regulator and plays a vital role in placenta development and function.(1, 2) DNA methylation is known to change with increasing gestational age (3-5) and changes in placental DNA methylation are associated with multiple maternal, gestational and placental related complications, like pre-eclampsia, gestational diabetes mellitus, preterm birth and intra-uterine growth restriction (6-12). Therefore, the study of placental DNA methylation potentially provides more insight in normal placental development and underlying pathophysiology of pregnancy related diseases and can be used to develop both gestational clock-based methylation profiles as well as disease specific biomarkers.

Usually, obtaining placental tissue during pregnancy requires invasive procedures (e.g. chorionic villus sampling). However, cfDNA originated from placental trophoblasts can be found in maternal plasma providing the opportunity to study placental DNA methylation in a non-invasive manner. Currently, cfDNA is already widely used for prenatal testing of fetal aneuploidies.(13) In addition, different studies have shown an increase in the level of (placenta-derived) cfDNA in pregnancies complicated by pre-eclampsia.(14-19) However, since cfDNA is derived from dying cells, multiple factors including acute exercise and obesity can have an impact on maternal cfDNA quantity affecting the placenta-derived fraction as well.(20, 21) Specificity of cfDNA as a biomarker for pregnancy related diseases could be improved by identifying disease-specific DNA methylation differences, ideally leading to biomarkers with the potential to identify women at risk of developing associated diseases at an early stage.

There are different methods to study genome-wide DNA methylation. Whole-genome bisulfite sequencing (WGBS) is able to reach >90% coverage of all cytosine-phosphate-guanine (CpG) sites in the human genome, but its use remains limited due to its high costs and technological challenges. Reduced representation bisulphite treatment or Illumina microarray technology are widely used, but are restricted to a limited subset of CpGs.(22) Therefore, the recently developed MeD-seq technique is a promising alternative. MeD-seq focusses CpG methylation analysis to only the methylated regions of the genome, therefore requiring less sequencing depth as compared to WGBS but allows for genome-wide methylation profiling of more than half of all potentially methylated CpGs.(23) Additionally, MeD-seq requires only a

limited amount of input DNA (24) making it a suitable technique to study methylation patterns using the relatively low levels of cfDNA available in clinical practice.

In summary, research gaps exist regarding cfDNA methylation changes related to gestational age in normal pregnancies, and how this is affected by different pregnancy related diseases. This is the first study to investigate gestational age and pregnancy related disease specific DNA methylation changes in cfDNA in all trimesters in a genome-wide manner using MeD-seq.

**Primary Objective:**

1. Identify pregnancy related disease specific methylation profiles in cfDNA in maternal plasma, with the potential to identify women at risk of developing pregnancy related complications including pre-eclampsia, intra-uterine growth restriction and pre-term birth.
2. Identify genes or genetic pathways involved in the development of maternal, gestational and placental related complications.

**Secondary Objective:** Identify trimester-specific methylation profiles (identified at 11 weeks, 22-24 weeks and 30-32 weeks of gestation and at time of delivery) in cfDNA in uncomplicated pregnancies to determine gestational age specific reference profiles and identify genes or genetic pathways involved in normal placental development.

**The Rotterdam Periconceptie cohort (Predict studie)**

The Predict study is a single center prospective longitudinal cohort study (Predict study, METC 2004-227) aiming to gain more insight in the development and underlying causes of fertility problems and pregnancy complications. The overall goal is to identify parameters able to predict the occurrence of these pathologies before or in the beginning of pregnancy, to ultimately prevent these complications.(25, 26)

**Implementation**

During thirty months, after approval of this addendum and informed consent from the participants, additional blood draws will be performed at the same day as the ultrasound visits for the Predict study around 11, 22-24 and 30-32 weeks of gestation and during delivery if the delivery takes place at the Erasmus MC. This blood draw at 11 weeks of gestation will be combined with the current blood draw in

first trimester which is already being performed within the Predict study. Two extra tubes of blood will be collected in CellSave tubes and processed into plasma to be stored at -80°C until isolation of cfDNA takes place.

Our primary outcome are differentially methylated regions (DMRs) found in these cfDNA methylation profiles between uncomplicated controls versus women who develop pregnancy related diseases like pre-eclampsia, intra-uterine growth restriction and pre-term birth. It is not possible to make a power calculation beforehand because it is not known what the methylation profiles will look like. However, based on previous experiments to generate reference profiles using MeD-seq, the number of reliable DMRs stabilizes when having a sample size of  $\pm 8-9$  samples. The incidence of the above mentioned pregnancy related diseases in Europa are 4-5% for pre-eclampsia (27), 9% for preterm birth (28) and 8-10% for intra-uterine growth restriction (29). We aim to include 10 pre-eclampsia cases and account for 20-25% loss to follow up, including loss because of miscarriages. Therefore we intend to include 300 women in total. Because of the higher incidence of preterm birth and intra-uterine growth restriction it is likely this cohort will comprise at least 10 women affected by these complications as well.

We will identify specific DMRs in cfDNA from maternal plasma determined using MeD-seq and perform pathway analyses of genes associated with identified DMRs involved in associated diseases using <http://geneontology.org> in collaborations with the department of Developmental Biology, [name], Erasmus MC.

## LIST OF ABBREVIATIONS AND RELEVANT DEFINITIONS

|                          |                                                                                                                                             |
|--------------------------|---------------------------------------------------------------------------------------------------------------------------------------------|
| cfDNA             | Cell free DNA                                                                                                                               |
| CpG               | Cytosine-phosphate-Guanine                                                                                                                  |
| DMR               | Differentially Methylated Region                                                                                                            |
| DOHaD             | Developmental origins of health and disease                                                                                                 |
| DTA               | Data Transfer Agreement                                                                                                                     |
| Exception consent | Form Care for data Template , in Dutch: Formulier uitzondering toestemming                                                                  |
| FDR               | False Discovery Rate                                                                                                                        |
| IC                | Informed Consent                                                                                                                            |
| MeD-seq           | Methylated DNA sequencing                                                                                                                   |
| MTA               | Material Transfer Agreement                                                                                                                 |
| NWTC              | Non-WMO Review Committee; in Dutch: Niet WMO Toetsingscommissie                                                                             |
| UAVG              | Dutch Act on Implementation of the General Data Protection Regulation;
in Dutch: Uitvoeringswet Algemene Verordening Gegevensbescherming |
| WMO               | Medical Research Involving Human Subjects Act, in Dutch: Wet Medisch-wetenschappelijk Onderzoek met Mensen                                  |

## PROTOCOL SUMMARY

DNA methylation is essential for normal placental development and function. Previous studies have shown differences in placental DNA methylation related to gestational age and in placenta-related diseases. Unfortunately, placental methylation profiles early and mid-gestation are largely understudied since obtaining placental tissue during pregnancy is invasive. A promising alternative to noninvasively study placental DNA methylation is placental-originated cell free DNA (cfDNA) in the maternal circulation, which is currently widely applied for non-invasive prenatal testing (NIPT). However, specificity of cfDNA to study placental DNA is hampered by the presence of circulating (so called background) maternal cfDNA.

In this study, we aim to identify differentially methylated regions (DMRs) in placental tissues between the three different trimesters of pregnancy using the recently developed Methylated DNA Sequencing (MeD-seq) technology. MeD-seq allows the study of DNA methylation genome-wide and provides a more extensive coverage of the genome compared to most other techniques. Importantly, it is compatible with low concentrations of circulating cfDNA. After identification of trimester-specific DMRs, the next step will involve analyses of underlying genes or genetic pathways related to these DMRs. Insight into dynamics of placental methylation and involved genes throughout pregnancy could increase our understanding of normal placental development. Moreover, a reference database of longitudinal placental methylation patterns of (uncomplicated) pregnancies based on direct placental tissues could serve as a blue-print to help distinguish the placental derived cfDNA fraction from the background maternal cfDNA in future studies, improving specificity of specific placental cfDNA as a non-invasive placental marker.

Placental samples will either be obtained via the Fetal Biobank Amsterdam (retrospectively), abortion clinics, including but potentially not limited to Gynaikon Kliniek Rotterdam and Bea & Bloemenhovekliniek (prospectively), and the Erasmus MC (both retrospectively and prospectively). The majority of first and second trimester samples from the Fetal Biobank Amsterdam and the Erasmus MC originate from pregnancies complicated by congenital defects or obstetric complications such as immature birth. Since, placental samples of uncomplicated pregnancies are needed as reference, first and second trimester samples from uncomplicated pregnancies terminated for social indications will be collected at abortion clinics. Third trimester placentas of both complicated and uncomplicated pregnancies will be collected at the Erasmus MC. DNA will be isolated from placental biopsies and subsequently be sequenced using MeD-seq. Based on previous experiments generating reference profiles from different tissues using MeD-seq, we aim to include a minimum of 10 samples per trimester both retrospectively and prospectively.

Participants retrospectively recruited either already provided informed consent to use placental tissue for scientific research, or these women made no objection to the use of residual material at the time of their outpatient clinic appointment during pregnancy. For prospectively collected placental tissues obtained via an abortion clinic, informed consent will be asked by an independent nurse or medical doctor working at the abortion clinic after opting for termination of the pregnancy. These tissues will be collected anonymously and would otherwise be discarded after the procedure. For participants prospectively

## Placental Methylation

recruited in first, second or third trimester at the Erasmus MC, informed consent will be asked by a member of the research group and tissues will be coded before use. Since only residual tissues will be obtained and used, participants will not undergo any additional procedures.

### 1. Introduction and rationale

The developmental origins of health and disease (DOHaD) hypothesis is supported by accumulating evidence showing the importance of the gestational environment for fetal development as well as for health outcomes later in life (1-3). Epigenetic mechanisms, of which DNA methylation is the most studied, have been proposed to play a role in affecting developmental programming (1-3) and are essential for normal placental development and function (4, 5). Impaired placentation has been associated with multiple adverse pregnancy outcomes. We and others have shown differentially methylated regions (DMRs) in postpartum placentas in pregnancies affected by a range of obstetric complications, including preeclampsia, intra-uterine growth restriction and preterm birth. This indicates a role for epigenetic mechanisms in disease development, either as cause or consequence. (6-14)

Placental methylation profiles early and mid-gestation are largely understudied due to the impossibility to non-invasively investigate placental tissue during pregnancy. Previous studies using tissues from elective abortions showed that placental DNA methylation in general increases with advanced gestational age (15-17). A promising alternative to study placental DNA methylation noninvasively already during pregnancy is by use of so called cell free DNA (cfDNA) originating from turnover and spill of placental cell types into the maternal circulation. Currently, cfDNA is already widely used for non-invasive prenatal testing for chromosomal aneuploidies as part of prenatal screening.(18) However, on average only 13% (range 3-30%) of total cfDNA within the maternal circulation originates from the placenta (19), with the remaining cfDNA originating from maternal tissues, hampering specificity of selection and detection of placental DNA methylation.

From the different methods to study genome-wide DNA methylation we will use the recently developed MeD-seq technology which focusses on regional changes in DNA methylation, requiring less sequencing depth as compared to whole-genome bisulfite sequencing while providing a more extensive coverage of the genome as compared to most other techniques.(20, 21) Besides, MeD-seq requires a limited amount of input DNA and is therefore one of the few technologies compatible with the low cfDNA levels available in clinical practice.(22)

Since no placental DNA methylation studies have yet been performed using MeD-seq, no suitable (technique-specific) reference methylation profiles per trimester exist. Here, we aim to identify trimester-specific DMRs in placental tissues in uncomplicated and complicated pregnancies using MeD-seq. Second, we intend to identify underlying genes or genetic pathways related to identified DMRs, hereby increasing our understanding of normal placental development. Moreover, identified placental DNA methylation profiles could serve as a blue-print to subsequently help distinguish the placental derived fraction from the maternal one in total cfDNA in the maternal circulation during pregnancy, improving specificity of cfDNA as placental marker in future studies into cfDNA using MeD-seq (Figure 1). This could lead to numerous applications, including the identification of disease-specific DNA methylation changes with the potential to be used as novel noninvasive biomarkers for early prediction of placenta-related diseases in future studies.

[figure not shown]

Figure 1: Schematic overview of how a reference database of placental methylation patterns based on direct placental tissues could serve as a blue-print to help distinguish the placental derived fraction in total maternal cfDNA in future studies. CpG = cytosine-phosphate-guanine site; cfDNA = cell free DNA

## 2. Objective(s)

### Primary objective:

- 1) Identify trimester-specific DMRs in placental tissues of uncomplicated and complicated pregnancies using MeD-seq;

### Secondary objectives:

- 2) Identify underlying genes or genetic pathways related to identified DMRs involved in (ab)normal placental development.
- 3) Identify placental DNA methylation profiles to specifically distinguish the placental derived fraction from the maternal one in total cfDNA in the maternal circulation during pregnancy in future studies using MeD-seq.

## 3. Study type

### 3.1 Study type:

- ☐ Retrospective
- ☐ Prospective
- ☒ Combination Retrospective/Prospective

### 3.2 Check all the applicable boxes:

## Placental Methylation

- ☒ Medical records (re-use of data from healthcare, including AI)
- ☐ Case report
- ☐ Re-use data from research
- ☐ Evaluations of quality of healthcare (retrospective)
- ☒ Research with additional use of residual material from regular healthcare
- ☒ Research with re-use of human materials from research or existing biobank
- ☐ Research with human materials without biobank
- ☐ De novo biobank (human material obtained without burdensome or invasive procedures)
- ☐ Post marketing survey research with medical devices
- ☐ Phase IV research
- ☐ Healthcare evaluation research (prospective)
- ☐ Medical devices
- ☐ In Vitro Diagnostic Tests
- ☐ Other research, *describe*

## 4. Study population

### 4.1 Population (base)

Placental samples will either be obtained via the Fetal Biobank Amsterdam (retrospectively), abortion clinics, including but potentially not limited to Gynaikon Kliniek Rotterdam and Bea & Bloemenhovekliniek (prospectively), and the Erasmus MC (both retrospectively and prospectively). The majority of first and second trimester samples from the Fetal Biobank Amsterdam and the Erasmus MC originate from pregnancies complicated by congenital defects or obstetric complications such as immature birth. Since, placental samples of uncomplicated pregnancies are needed as reference, first and second trimester samples from uncomplicated pregnancies terminated for social indications will be collected at abortion clinics. Third trimester placentas of both complicated and uncomplicated pregnancies will be collected at the Erasmus MC.

### 4.2 Inclusion criteria

In order to be eligible to participate in this study, a subject must meet all of the following criteria:

- For samples retrospectively collected: residual placental tissue available at the Fetal Biobank Amsterdam or Erasmus MC from singleton pregnancy;

- For samples prospectively collected at the Erasmus MC or abortion clinic:
  - o Participant has to be at least 18 years of age
  - o Singleton pregnancy
  - o Participant is willing and able to give written informed consent
  - o Additional for abortion clinic: voluntarily chosen for elective, surgical abortion for social indication, before potential participation in this study is discussed.

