### 4.3 Exclusion criteria

Potential participants undergoing an abortion at the abortion clinic will be excluded from study participation if they are infected with HIV, hepatitis B or other blood borne infectious diseases. This is an exclusion criteria set by the abortion clinic for participation in any research with residual tissues for security reasons.

Additionally, samples retrospectively collected at the Erasmus MC for which no explicit informed consent is available, will be excluded if they have not seen a (research) nurse during their pregnancy to discuss the potential use of residual tissue or when there is known objection against use of material for research purposes in the Erasmus MC 'database bezwaren'.

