### 4.4 Sample size calculation

Our primary outcomes are DMRs in placental DNA between different trimesters. Since no placental methylation studies have been performed using MeD-seq, it is unknown what the methylation profiles will look like.

Power calculations are therefore not possible. Based on previous experiments to generate reference profiles using MeD-seq in other tissues, the number of reliable DMRs stabilizes when having a sample size of a minimum of 10 samples. Therefore, we aim to include at least 10 different samples per trimester both retrospectively and prospectively.

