## 5. Methods

- 5.1 *Please describe how you do conduct research and which methods are used, e.g. questionnaires, human material collection, extraction of data from medical records, analysis of images, the use of an app/medical device/diagnostic test, clinical tests to be performed, etc. Include information on frequency, duration, volumes, if a Data Management Plan is available (then please upload DMP).*

Placenta samples from all three trimesters from both complicated and uncomplicated pregnancies will be obtained in multiple ways as described earlier: via the Fetal Biobank Amsterdam (retrospectively), abortion clinics (prospectively) and the Erasmus MC (both retrospectively and prospectively). After sample collection, DNA will be isolated from placental biopsies. MeD-seq technology will be used to investigate DNA methylation profiles between different trimesters in both complicated and uncomplicated pregnancies. Custom Python scripts will be used to process the acquired DNA methylation profiles. Raw data files (fastq) will be filtered to be able to distinguish methylation data from background data and will be mapped to the human genome (hg38) using bowtie. To subsequently analyse DMRs, we will generate both regional (promoter, gene body and cytosine-phosphate-guanine (CpG) Island regions) as genome-wide methylation scores. For the genome-wide analysis, a sliding window technique will be used to detect DMRs. The Chi-squared test will be used for statistical testing with either the False Discovery Rate (FDR) or Bonferroni correction for multiple testing. A FDR or Bonferroni adjusted p-value <0.05 will be considered significant. After DMRs are determined, Z-score transformation of the read count data will be applied for unsupervised hierarchical clustering analysis. Pathway analyses will be performed using <http://geneontology.org>.

- 5.2 *Standard clinical care versus extra for research:  
Indicate which of the methods are part of standard clinical care and which tests and/or visits are extra for research purposes i.e. not standard clinical care.*

Since only residual tissues will be used, participants will not undergo any additional procedures. The placentas would otherwise be discarded. Sample collection and MeD-seq is only for research purposes.

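### Sub-study 2 sets no chromosomal criterion for placental tissue, so copy-number differences can appear as trimester- or complication-related DMRs

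*Protocol*

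**What the plan says.** Sub-study 2, section 4.2, requires of retrospective material only that it be "residual placental tissue available at the Fetal Biobank Amsterdam or Erasmus MC from singleton pregnancy". Prospective samples need adult age, a singleton pregnancy and consent, plus an elective surgical abortion for social indication at the abortion clinics. Section 4.3 excludes abortion-clinic participants "if they are infected with HIV, hepatitis B or other blood borne infectious diseases", and some retrospective hospital samples on consent grounds. Neither section mentions a chromosomal abnormality.

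On sources, section 4.1 says that most first and second trimester biobank and hospital samples "originate from pregnancies complicated by congenital defects or obstetric complications such as immature birth". Section 9.1 adds that the retrospective hospital pregnancies of those trimesters mostly ended in termination for a birth defect or in spontaneous immature delivery. The uncomplicated references for the same trimesters come from the abortion clinics. Third trimester placentas, complicated and uncomplicated, come from the hospital.

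On size and analysis, section 4.4 states: "we aim to include at least 10 different samples per trimester both retrospectively and prospectively". Section 5.1 scores regions and sliding windows and then says: "The Chi-squared test will be used for statistical testing with either the False Discovery Rate (FDR) or Bonferroni correction for multiple testing". The level is fixed by "A FDR or Bonferroni adjusted p-value <0.05 will be considered significant". That the data are counts is clear from the next step: "Z-score transformation of the read count data will be applied for unsupervised hierarchical clustering analysis". The main endpoint (section 8.1) is trimester-specific DMRs in uncomplicated and complicated pregnancies.

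**The concern.** In a read-count assay, a region can show more reads because more of it is methylated or because more copies of it are present. A trisomic placenta has three copies where others have two, so every region on that chromosome yields about half as many reads again with no change in methylation.

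This would matter less if such samples were spread evenly over the groups. The sources make imbalance plausible: the complicated first and second trimester samples come largely from pregnancies with congenital defects or immature birth, and their comparators come from social-indication abortions. Because the mix of sources also changes by trimester, the distortion could appear as a trimester difference as well as a complication difference. It would then enter the pathway analysis (section 8.2) as genes of abnormal placental development.

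A better test would not remove the bias, because the difference in counts is real but is not methylation. Nor does the ten-sample rule. Sub-study 3, section 4.4, accepts that genomic variation can be mistaken for a DMR and relies on ten or more individuals to filter it out. That suits variation scattered across people, not variation that eligibility concentrates in one group.

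Timing matters too. Biobank and abortion-clinic samples arrive anonymously (sections 10.1 and 11.3), so a diagnosis not used at selection cannot be looked up later.

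**Working it through.** The protocol gives no power or error figure to reproduce; section 4.4 says a power calculation is not possible. The check is therefore of mechanism and size.

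**Inputs from the protocol.** At least 10 samples per trimester (sub-study 2, 4.4). Chi-squared test with FDR or Bonferroni at 0.05 (5.1). Placental share of maternal cfDNA 13%, range 3-30% (sub-study 2, section 1).

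**Assumptions.** k of n = 10 samples in one compared group carry the same trisomy and none in the other does. R is the mean number of reads per region per unaffected sample. Library sizes are equal. Counts are Poisson and pooled over each group's samples. The protocol gives neither k nor R, and does not say how samples are combined in the chi-squared test.

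**Step 1, group shift in tissue.** Ratio = 1 + 0.5k/n. For n = 10 this is 1.05, 1.10, 1.15 and 1.25 at k = 1, 2, 3 and 5. With n = 20, one affected sample gives 1.025.

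**Step 2, chance that a region on that chromosome is flagged.** Expected z = 10R(0.05k) / sqrt(10R(2 + 0.05k)). The threshold p<1e-6, which is Bonferroni over 50,000 tests (0.05/50,000), needs |z| > 4.892. The chance is about Φ(z − 4.892).

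| k of 10 | R | Expected z | Share of regions at p<1e-6 |
|---|---|---|---|
| 1 | 1000 | 500/√20,500 = 3.49 | 8% |
| 2 | 1000 | 1000/√21,000 = 6.90 | 98% |
| 1 | 200 | 100/√4,100 = 1.56 | 0.04% |
| 2 | 200 | 200/√4,200 = 3.09 | 3.5% |
| 3 | 200 | 300/√4,300 = 4.58 | 38% |
| 3 | 50 | 75/√1,075 = 2.29 | 0.5% |

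FDR at the same level rejects at least whatever Bonferroni rejects, so it would flag no fewer.

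**Step 3, reads needed.** Setting expected z equal to the Bonferroni critical value gives pooled reads = z²(FC + 1)/(FC − 1)², where FC is the group ratio. At that depth about half the regions are flagged. For 100,000 tests (z² about 25.27):

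- k = 1: 20,717 pooled, about 2,072 per sample
- k = 2: 5,306 pooled, about 531 per sample
- k = 3: 2,415 pooled, about 242 per sample
- k = 5: 910 pooled, about 91 per sample

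The number of tests matters little. For k = 1 the pooled figure runs from 17,087 (10,000 tests) to 24,368 (1,000,000 tests).

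**Step 4, the same on the cfDNA of sub-study 3.** One trisomic pregnancy shifts its own sample by 0.5f, where f is the placental fraction: 1.5%, 6.5% and 15% at f = 3%, 13% and 30%. The scale comparable with Step 1 is the group mean, 0.5f/10: +0.15%, +0.65% and +1.5%. At 13%, one affected sample in 10 would need about 1.2 million pooled reads per window at 100,000 tests, and three in 10 about 134,000.

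**The case against.** The strongest reply is that nothing in the protocol says any sample is aneuploid. Congenital defects and immature birth need not be chromosomal, and no share is given. That stands, and it makes the point conditional. One affected sample does little unless counts are high, and the larger effects need several samples with the same extra chromosome.

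Three stronger readings are tempting and are not supported. A reader might infer that trisomic placentas can sit only in the complicated first and second trimester groups. In fact no chromosomal criterion applies to abortion-clinic or third trimester samples either, so the documents make imbalance plausible, not exclusive. A reader might infer that the placental reference for cfDNA work is contaminated. The protocol summary describes that reference as coming from uncomplicated pregnancies, although the introduction is looser. A reader might put sub-study 3 on an equal footing, since it lists no exclusions and sets no condition on the NIPT result. Step 4 shows a far smaller effect there. Its cases are also not selected for congenital defects, and ten patients per group are held back for internal validation, so a chance case in the training set should not replicate.

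It can also be said that copy-number handling belongs to the bioinformatic pipeline or an unseen analysis plan. That is fair for the correction method. It does not cover eligibility, which the protocol fixes and which anonymity makes hard to repair later.

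Finally, exclusion narrows a study that means to include complicated pregnancies. That also stands, and separate analysis is an acceptable alternative.

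**Conclusion.** The point holds for sub-study 2 in conditional form. Its eligibility admits chromosomally abnormal placentas, its sources make an imbalance between compared groups plausible, and the analysis as described would not tell extra copies from extra methylation. False trimester- or complication-related DMRs can follow; the documents do not show that they will.

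The group mean on the affected chromosome moves by about 5% per affected sample in 10. This is material when several samples share a trisomy or read counts are high, and small for a single case. These figures rest on pooled Poisson counts, equal library sizes, and assumed numbers of affected samples and read depths. They also assume that no undescribed step already corrects for copy number.

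For sub-study 3, a group shift of +0.15% to +1.5% per affected sample in 10 is not a material problem.

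**What to change.** Add to sub-study 2, section 4.3, that samples from pregnancies with a known chromosomal abnormality are excluded from the DMR comparisons. Apply this to the diagnosis held by the biobank or the hospital, before the anonymous biobank sample is released and before the hospital sample is coded. This presumes that the sources hold a diagnosis, as section 4.1's description of them suggests. If such pregnancies are wanted, name them as a separate group and analyse them apart.

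Add to section 5.1 a check of each sample's per-chromosome read share against a threshold stated in advance, made before DMR calling. It uses MeD-seq data that will exist anyway, and it covers samples with no recorded diagnosis. Fixing the threshold beforehand keeps it from becoming a data-driven exclusion.

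The cost is protocol wording and one quality check. Some complicated first and second trimester samples would have to be replaced, and the main results would no longer describe aneuploid pregnancies.

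As an optional companion edit, sub-study 3, section 4.3, could exclude women with an aneuploid NIPT result.
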